### Sample Size

A sample size of approximately 10,000 patients, (5000) pre- and (5000) post-intervention, is anticipated. Based on prior studies it is expected that 80% (4000 patients/group) will have follow-up data from the EMR or insurer claims. With this sample size we will be able to estimate safety event rates for each study period to ±0.33% with 95% confidence (assuming an event rate of 1%). Based on our prior studies, we expect a hospitalization rate of 53% and an objective cardiac testing rate of 83% among hospitalized patients during the preintervention period [16,21]. This study will be adequately powered to detect reductions in hospitalization and objective cardiac testing rates of <5%, with 90% power at the 5% two-sided level of significance. We anticipate larger effects [16,17,22].

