### Study Timeline

Pre- and post-HEART Pathway ADP implementation cohorts will each accrue patients with acute chest pain for 1 year, with a 3-month wash-in period (Figure 1). Data will be collected electronically from all patients using health system electronic medical records (EMRs), and claims data from insurers will be used on a subset of patients insured by Blue Cross Blue Shield (BCBS) of North Carolina (the largest insurer in the state), MedCost, or North Carolina Medicaid.

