### Statistical Analyses

Logistic regression models, which include potential patient-level confounders such as age, sex, race, ethnicity, insurance status, and ACS risk factors in addition to the intervention indicator, will be used to assess the effect of the HEART Pathway intervention on hospitalizations (and other dichotomous outcomes such as objective cardiac testing and recurrent ED visits). As secular trends represent a threat to internal validity (observed differences between groups could be from time trends rather than the intervention), we will include the time since the start of the study in the models, as well as the time by intervention interaction. This will allow us to assess the effect of the HEART Pathway implementation on the proportion of patients hospitalized, as well as its effect on the time trend after implementation.

Continuous outcomes will be analyzed using multiple linear regression models including potential confounders, time, the intervention indicator (pre- or post-HEART Pathway implementation), and the time by intervention interaction as described above. LOS tends to be skewed, so we will use some transformation (log, rank, etc) in the analyses if necessary. Residuals will be examined to ensure the model assumptions (linearity, homoscedasticity, and normality) are met. Not all patients will have electronic follow-up data. The default assumption will be that patients without follow-up data from the EMR, insurers, or Social Security Death Masterfile did not suffer adverse events. Sensitivity analyses will be used to assess the impact of missing data on our results. The analyses will be repeated assuming all patients with missing follow-up data had follow-up events (hospitalization, cardiac testing, etc). Multiple imputation will be used to conduct sensitivity analyses that generate complete datasets under a variety of assumptions regarding the rates of outcomes in the two periods. All analyses will be performed using SAS 9.4 (Cary, NC). *P*<0.05 will be considered significant.

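### The stated 90% power for reductions under 5 points fits an unadjusted pre-post comparison, not the time-adjusted model the protocol plans to use

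*Protocol article*

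**What the plan says.** The protocol article, Sample Size, expects 5000 patients in each period ("A sample size of approximately 10,000 patients, (5000) pre- and (5000) post-intervention, is anticipated"), of whom 80%, or 4000 per period, should have follow-up data. For the pre-implementation period, "we expect a hospitalization rate of 53"%, together with "an objective cardiac testing rate of 83% among hospitalized patients during the preintervention period". It then states that the study is "adequately powered to detect reductions in hospitalization and objective cardiac testing rates of <5%, with 90% power" at the two-sided 5% level, and adds that larger effects are anticipated. No test is named for this power statement.

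Statistical Analyses specifies logistic regression with patient-level confounders and an intervention indicator. Because secular trends threaten validity, "we will include the time since the start of the study in the models, as well as the time by intervention interaction". Study Timeline says the two cohorts will "each accrue patients with acute chest pain for 1 year, with a 3-month wash-in period". The primary outcome is hospitalization at 30 days.

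**The concern.** In a single before-after design, calendar time and period carry much the same information: early patients are all pre, late patients are all post. A model that estimates a time trend together with the intervention effect therefore has far less information on the intervention than a comparison of two proportions on the same patients. The Sample Size section makes no visible allowance for this.

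Readers will use the power statement to interpret a null or borderline primary result. If it describes a different analysis from the planned one, a real reduction of 4-5 points could easily be non-significant while the protocol tells the reader it would very probably have been detected.

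**Working it through.** **Inputs.** Two-sided alpha 0.05, power 90%, baseline hospitalization 53%, baseline testing 83% of hospitalized patients, 5000 per period or 4000 with follow-up (all from Sample Size). Two 12-month cohorts and a 3-month wash-in (Study Timeline). Model terms from Statistical Analyses. Figure 1 is not available, so the wash-in was treated both ways: as a gap between the cohorts and as no gap. My assumptions, not the article's: the 5% is in absolute points, accrual is uniform, and true trends are flat within each period.

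**Step 1: reproduce the stated figure.** Unadjusted detectable drop = (1.960 + 1.2816) × √[(p₁q₁ + p₂q₂)/n].
- n = 4000: 3.2415 × √[(0.2491 + 0.2500)/4000] = 3.6 points
- n = 5000: 3.2415 × √[(0.2491 + 0.2500)/5000] = 3.2 points

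For 53% to 48%, the crude standard error with n = 4000 is √[(0.2491 + 0.2496)/4000] = 0.01117, so z = 0.05/0.01117 = 4.48 and power = Φ(4.48 − 1.96) = 99.4%. With n = 5000, z = 5.01 and power is 99.9%. The stated figure is therefore right, and even conservative, for an unadjusted comparison.

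**Step 2: variance under the planned model.** With uniform accrual over one year, a line fitted within a period has, at distance d years from that period's midpoint, a variance (1 + 12d²) times that of the period's mean. The inflation of the level-change variance over the crude difference is the average of the two periods' factors.
- No gap, evaluated at implementation: d = 0.5 on both sides, (4 + 4)/2 = 4.0
- 3-month gap, evaluated at the start of the post period: d = 0.75 and 0.5, (7.75 + 4)/2 = 5.9
- 3-month gap, evaluated mid-gap: d = 0.625 on both sides, 5.7

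**Step 3: power for 53% to 48%.** Divide the crude z by the square root of the inflation.

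| Patients per period | No gap (×4.0) | 3-month gap (×5.9) |
|---|---|---|
| 4000 | 4.48/2.00 = 2.24; 61% | 4.48/2.42 = 1.85; 45% |
| 5000 | 5.01/2.00 = 2.50; 71% | 5.01/2.42 = 2.07; 54% |

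The logistic information matrix gives the same values within about a point. Evaluating mid-gap raises the gap column by only about a point (47% and 55%).

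**Step 4: drop detectable with 90% power (logistic model).** With 4000 per period: 7.3 points (no gap) to 8.8 points (gap). With 5000: 6.5 to 7.9 points.

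**Step 5: other contrasts from similar models**, power for the same 5-point drop across both sample sizes and both wash-in readings:
- Common slope, interaction dropped: inflation 4.0 to 5.7; power 47-71%. Removing the interaction alone does not restore power.
- Joint 2-df test of level and slope: 37-60%.
- Effect at the middle of the post period against the extrapolated pre-trend: inflation (1 + 13)/2 = 7 to (1 + 19.75)/2 = 10.4; power 28-47%.
- Intervention coefficient with time counted uncentred from study start: inflation (4 + 28)/2 = 16 to (4 + 37.75)/2 = 20.9; power 16-24%, with 13-17 points needed for 90% power.

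**Step 6: objective testing.** If non-hospitalized patients have no testing (an assumption), the overall baseline is 0.53 × 0.83 = 44%. The unadjusted detectable drop is 3.6 points (4000) or 3.2 (5000). For the level change at implementation, solving the Step 1 formula with the Step 2 inflation gives 7.1-8.6 points with 4000 and 6.4-7.7 with 5000; for example 3.2415 × √[4 × (0.2464 + 0.2331)/4000] = 7.1. Power for a 5-point drop is 47-72% overall, and 38-63% if testing is analysed among hospitalized patients only (0.53 × 4000 = 2120 or 0.53 × 5000 = 2650 per period).

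**The case against.** The other side has several fair points.

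- *The arithmetic is not wrong.* The figure reproduces for two proportions, and Sample Size does not say it refers to the time-adjusted coefficient. This stands. The defect is a mismatch between the power statement and the planned model, not a slip in calculation. It is still visible within the article, because the model is fixed in the preceding section, so it is not merely a detail left to a fuller plan.
- *There is no single power under the planned model.* This also stands. The protocol fixes neither the centring of time nor the point at which the effect is evaluated. Centring time separately within each period would bring the inflation back to 1 and power above 99%, but that contrast no longer removes a common secular trend, which is the stated reason for including time.
- *The lower figures use 4000 per period.* Statistical Analyses by default counts patients without follow-up as free of adverse events, which suggests the main analysis may keep about 5000. On that reading the range is 54-71%, still well below 90%.
- *Covariates may sharpen the estimate.* The article gives no figures for this, and offsetting a 4- to 6-fold inflation is not expected.
- *Larger effects are anticipated.* A reader might infer from the low power that the study is too small or cannot succeed. The documents do not support that. Accrual is set by calendar, 10,000 is an anticipated number, and with time centred at implementation a 10-point drop has about 96-99.9% power. The opposite inference, that ample power is assured, is not supported either. Sample Size gives no size for the anticipated effect; the 21.3 and 12.1 points in Preliminary Data are early-discharge and testing differences from the earlier randomized trial. With uncentred time, a 12.1-point drop would have only 65-85% power.

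**Conclusion.** The point holds as a mismatch between the stated power and the planned analysis. The claim of 90% power below 5 points applies to an unadjusted pre-post comparison (3.2-3.6 points). For the time-adjusted level change at implementation, power for a 5-point drop in hospitalization is about 45-61% with 4000 per period and 54-71% with 5000, and 90% power needs about 6.5-8.8 points. These figures rest on uniform accrual, flat true trends, absolute differences and time centred at implementation; the spread reflects follow-up and whether the wash-in is a gap. They belong to that contrast only, but none of the contrasts tried that adjust for a secular trend reaches 90%. The sentence should be corrected. It is not a fatal flaw, because no sample size decision depends on it and larger effects are expected.

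**What to change.** In Statistical Analyses, define the primary contrast as the level change at implementation, with time centred there. In Sample Size, replace the power sentence with wording such as:

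> For the time-adjusted level change at implementation, 4000-5000 patients per period give 90% power for an absolute reduction in hospitalization of about 6.5-8.8 points, depending on follow-up and the wash-in gap; 3.2-3.6 points applies only to the unadjusted comparison.

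Give the matching figure for objective testing (about 6.4-8.6 points in all patients, from a 44% baseline), and state that 44% assumes no testing in patients who are not hospitalized.

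The cost is a few reworded lines and a less favourable stated figure. No extra patients and no change to accrual are needed.

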### Multidisciplinary Collaboration

To facilitate implementation, we have created the Wake Forest HEART Pathway Integration Team consisting of key stakeholders within health system leadership, medical school leadership, and across the disciplines of public health, medical informatics, cardiology, primary care, nursing, and emergency medicine. Through this collaborative effort we will not only engage key stakeholders in the integration of the HEART Pathway with education and care delivery at Wake Forest Baptist Health, but also gain great insights into the potential barriers and facilitators for widespread dissemination and implementation of similar evidenced-based health system quality improvement initiatives across US medical centers.

## Results

### Preliminary Data

To evaluate the HEART Pathway prior to implementation, we analyzed registry data from 1070 low-risk chest pain patients in an ED-based Observation Unit at Wake Forest Baptist Health. The HEART Pathway identified all 12 patients with major adverse cardiac events at 30 days (100% sensitivity, 95% CI 72-100%) and could have identified 879 of 1070 patients (82%, 95% CI 80-84%) for early discharge without objective testing [16]. Next, we analyzed data from the Myeloperoxidase In the Diagnosis of Acute Coronary Syndromes (MIDAS) Study [23], a multicenter cohort which included 991 participants with suspected ACS from 18 US EDs and data for HEART Pathway risk assessment. ACS was present in 220 of 991 patients (22% of the cohort). In this cohort, the HEART Pathway identified 218 of 220 patients (99% sensitivity, 95% CI 97-100%) with ACS (cardiac death, MI, or unstable angina) within 30 days and identified 200 of 991 patients (20%, 95% CI 18-23%) for early discharge [17]. A lower early discharge rate in MIDAS compared with our first study is explained by the higher prevalence of ACS events in the MIDAS cohort (22% vs 1%). Most importantly, the HEART Pathway had 99% sensitivity in this higher-risk population, suggesting it can be applied broadly to all patients undergoing ACS evaluation. Finally, we conducted the HEART Pathway Randomized Controlled Trial in which 282 adult patients with acute chest pain were randomized to risk stratification via the HEART Pathway ADP or usual care, based on American College of Cardiology/American Heart Association guidelines. In this trial, use of the HEART Pathway decreased objective cardiac testing at 30 days, reduced median LOS by 12 hours (9.9 vs 21.9 hours, *P*<.01), and increased early discharges. In the usual care group 97 of 141 patients had objective cardiac testing compared with the HEART Pathway group, which had testing in 80 of 141 patients (a difference of 12.1%, 68.8% vs 56.7%, *P*=.048). In the usual care group, 26 of 141 patients had an early discharge, while 56 of 141 had early discharge in the HEART Pathway group (a difference of 21.3%, 39.7% vs 18.4%, *P*<.001). No patients identified by the HEART Pathway for early discharge had adverse cardiac events within 30 days and the HEART Pathway was not associated with increased recurrent care [22].

### HEART Pathway Implementation

At the writing of this paper, data for this implementation study have been collected on >5000 patient encounters. The HEART Pathway has been fully integrated into health system EMRs, providing real-time decision support to our providers. Data infrastructure has been built such that patients meeting inclusion criteria are included in a registry, including 30-day electronic-surveillance data, which will be integrated with insurer claims data.

## Discussion

### Study Rationale

This paper describes the design of a prospective cohort study which will determine the effectiveness of the HEART Pathway ADP in safely reducing health care utilization (hospitalizations, objective cardiac testing, hospital length of stay, etc) among ED patients with acute chest pain. This study is timely given the high cost of delivering care to patients with acute chest pain and the current focus on delivering high-value care. The National Quality Strategy, outlined in the Affordable Care Act, focuses on increasing health care quality while simultaneously lowering costs [24]. To adapt to this changing health care landscape, health systems must develop effective methods of translating efficient evidence-based protocols, such as the HEART Pathway, into clinical practice [25-27].

Implementation of the HEART Pathway could improve the value of care for patients with chest pain by decreasing unnecessary health care utilization, false-positive/nondiagnostic testing, radiation, and costs [12]. Our prior analyses of the HEART Pathway, in combination with the HEART Score validation studies [14,15], provide efficacy data on over 7000 patients, and suggest that the HEART Pathway can have a large impact on avoiding testing in low-risk patients, yet retains high sensitivity when applied to higher-risk patients. Furthermore, the HEART Pathway’s ability to rapidly identify patients for early discharge and its overall ease of use make adoption in an ED setting feasible. Our experience with the HEART Pathway suggests that patients identified for early discharge will have significant reductions in index LOS and cost [22]. What is needed now is a prospective cohort study, as described in this paper, which will determine the effectiveness of the HEART Pathway by prospectively implementing it in a *real-world* clinical setting.

Nontraditional aspects of this study design include its pre-post interrupted time series design, multidisciplinary team implementation, CDS integrated into the EMR, automated prospective data capture, and electronic surveillance of outcomes (including partnering with insurers for claims data). These features will allow the passive accrual and surveillance of over 10,000 patients. Furthermore, this design will provide a template for others interested in pragmatic testing of care pathways within health systems.

### Limitations

The design of this study has some limitations when compared to a traditional randomized design. Secular trends and provider maturation effects are potential threats to the validity of our pre-post time series design. The electronic surveillance used in this study may increase loss-to-follow-up rates compared with traditional methods of follow-up. However, to determine effectiveness, the HEART Pathway must be utilized in an *all-comers* ED patient population. Randomized clinical trials, due to the consent process, have an inherent selection bias which can threaten the validity of an effectiveness study. Furthermore, given the size and scope of this implementation study, this design is more feasible and cost effective than a clinical trial.

### Conclusions

We hypothesize that this study will demonstrate that HEART Pathway implementation within a health system will result in meaningful reductions in health care utilization without compromising patient safety. We expect the HEART Pathway to decrease hospitalizations for comprehensive cardiac evaluations and the rate of objective cardiac testing among patients with a low pretest probability for ACS. In addition, our prior data suggest that the HEART Pathway will shorten hospital LOS for patients with acute chest pain, which should translate into significant cost savings and efficiency gains. Success of this study could provide a model for health systems to provide high-value care to 8-10 million patients who present to US EDs with acute chest pain each year.

## Abbreviations

ACS: acute coronary syndrome
ADP: accelerated diagnostic protocol
BCBS: Blue Cross Blue Shield
CDS: clinical decision support
ECG: electrocardiogram
ED: Emergency Department
EMR: electronic medical record
HEART: history/ECG/age/risk factors/troponin
LOS: length of stay
MI: myocardial infarction
MIDAS: Myeloperoxidase In the Diagnosis of Acute Coronary Syndromes
STEMI: ST-segment elevation myocardial infarction
